### Secondary outcomes

The National Institute of Health Stroke Scale (NIHSS) is used to evaluate the neurological function state of patients with stroke. This scale includes 11 items. The total score ranges from 0 to 42 points; and the higher the score, the more severe the nerve injury [26].The Brunnstrom staging (BS) scale for assessing movement function improvement in stroke patients. It is divided into stages I–VI; the greater the staging, the superior the restoration of function.Modified Ashworth scale (MAS) to evaluate variations in the patient’s muscle tone on a scale of 0, 1, 1 + , 2, 3, and 4 [27]; the higher the grade, the greater the muscle tone.The Modified Barthel Index (MBI) will be administered to the assessment of activities of daily living [28]. The total score is 100; a score ≤ 50 is classified as severe functional impairment, 50–75 as moderate functional impairment, 75–100 as mild functional impairment, and > 100 as no functional impairment.Central motor conduction time (CMCT) refers to the conduction time from the cerebral cortex to the alpha motor neurons in the anterior horn of the spinal cord. An intensity stimulus of 90% RMT will be applied to the patient’s seventh cervical spine (C7), and transmission time from C7 to the thumb short abductor muscle will be measured to calculate the difference between the transmission time from the scalp to the electrode piece and the transmission time from C7 to the electrode piece [29].Measuring serum biomarkers: the human MMP-9-ELISA kit (produced by ABclonal, China) will be used to quantify the level of MMP-9 expression in peripheral blood, and a human ProBDNF-ELISA kit (Biosensis, USA) will be used to detect the peripheral blood ProBDNF factor concentration [25]. The same protocol will be used to detect BDNF.

### Adverse events and safety monitoring

Adverse events will be monitored by a physical therapist and will include headaches in the stimulation area and hearing loss (due to coil noise). Earplugs will be placed on the patient during stimulation to prevent hearing damage. If localized pain or headache occurs, it is usually mild and can disappear quickly. The most serious side effect that can be triggered by TMS is seizures; however, the probability of occurrence is extremely low. Unsafe effects for TMS use by operators have not been reported since a long time. The patient’s vital signs, including heart rate, blood oxygen, and respiration, will be closely monitored during treatment.

### Sample size

We have calculated the sample size using the PASS 15 software. A literature search was conducted using FMA-UE as the primary indicator [8], specified as a two-sided test with *α* = 0.05 with a degree of certainty (test efficacy1-β) of = 0.8, and a total sample size of *N* = 60 cases was calculated. Considering a 20% dropout rate and the average distribution of each group, the total sample size was 76, with 19 individuals included in each group.

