This trial aims to investigate the clinical efficacy of LF-HF-rTMS on upper extremity motor function in convalescent stroke patients and to explore the mechanisms underlying its therapeutic effects. This study will assess the following: significant changes in clinical behavioral assessments and cortical excitatory parameters in patients with convalescent stroke after 10 interventions with rTMS, compared with that by sham and unilateral hemispheric stimuli. In addition, we will measure the concentrations of neuroplasticity mediators, serum BDNF, pro-BDNF, and MMP-9, and analyze their correlation with behavioral improvement.

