### Data analysis

Data analysis will be performed by the SPSS 26.0 statistical software, and statistical analysis of efficacy will be based on intention-to-treat analysis (ITT) principles.We will check whether the data is normally distributed using the Shapiro Wilk normality test. Nonparametric analysis such as chi-square test will be applied for the count data, and it will be expressed as rate or composition ratio. Nonnormal data will be tested using the Kruskal–Wallis test.Paired *t*-tests will be used for pre- and post-treatment comparisons of groups, one-way ANOVA for inter-group comparisons, and Bonferroni correction for post hoc comparisons between groups.Two-factor repeated measures ANOVA will be employed to investigate the impact of within-group factors (time points) and between-patient factors (subgroups) on outcomes and to analyze main and interaction effects.Pearson correlation analysis will be performed to investigate the correlation between cortical excitability (latency and CMCT) and motor function (FMA), the relationship between serum factors (BDNF, proBDNF, and MMP-9) and motor function, and the correlation between cortical excitability and serum factors.

A *P* value of < 0.05 will be regarded as statistically significant.

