### The choice of rTMS stimulus protocol

A recent animal study [33] suggested that high-frequency (20 Hz) rTMS promoted better muscle strength and motor coordination than low-frequency (1 Hz) rTMS in a mouse model of acute and subacute ischemic injury. Askin [34] and Kim et al. [35] also found that, in patients recovering from stroke, single-sided low-frequency and high-frequency rTMS were remarkably effective in improving motor function compared with those in conventional treatment. Considerable researches have confirmed the importance of low- and high- frequency rTMS alone in enhancing the upper limb functionality level after stroke, but clinical efficacy analysis favors the combination of low- and high-frequency rTMS over single stimulation [8, 36].

Long et al. randomly divided 62 early stroke patients into a group who received treatment of the unaffected side at 1 Hz combined with the treatment of the affected side at 10 Hz, a low-frequency group, and a sham stimulation group; they found the combined group to be more effective than the low-frequency group in bettering exercise levels in the upper extremities and that patients had better tolerability [8]. New research has also shown that double-target stimulation in patients with generalized anxiety disorder has stronger clinical efficacy than single-target stimulation in improving anxiety, depression, and insomnia [37]. However, there is a lack of research adopting combined applications as a treatment for paraplegic upper limb locomotion, especially during the recovery period. Therefore, the exact clinical efficacy of this combination still needs to be verified with a large number of studies. This trial will compare the clinical efficacy of the LF-HF-rTMS stimulation protocols on upper extremity dyskinesia in patients recovering from stroke.

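### The stated 80% power is for an unadjusted two-sided 0.05, but the contrasts in the aim are tested with Bonferroni correction, and over six pairs at 15 per arm none of the scenarios tried reaches 80%

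*Protocol article*

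**What the plan says.** All references are to the protocol article.

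- **Sample size.** The planning statement is "A literature search was conducted using FMA-UE as the primary indicator [8], specified as a two-sided test with"; the significance level named there is 0.05 and the power is 0.8. The result is "a total sample size of *N* = 60 cases was calculated". Allowing for 20% dropout, the total becomes 76, or 19 per arm. The section gives no effect size, SD, named test or multiplicity adjustment.
- **Background, final paragraph (aim).** Change after combined stimulation is to be judged "compared with that by sham and unilateral hemispheric stimuli". With four arms that makes three contrasts: combined versus sham, versus low-frequency and versus high-frequency.
- **Data analysis.** Arms are compared by one-way ANOVA, with "Bonferroni correction for post hoc comparisons between groups". The number of pairs is neither stated nor restricted.
- **The choice of rTMS stimulus protocol.** The planning source is described as a trial of 62 early stroke patients with a combined group, "a low-frequency group, and a sham stimulation group".

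**The concern.** The trial is sized at one alpha, and the contrasts that answer its question are tested at a stricter one. Four arms give six pairs, so Bonferroni over all of them leaves 0.05/6 = 0.0083 per pair. Unless N = 60 already allowed for this, which the text does not report, the stated 80% does not carry over to those contrasts.

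The planning source adds a second gap. As described, it had no high-frequency arm, so it supplies no effect for combined versus high-frequency. It also enrolled early stroke patients, whereas this trial requires a disease duration of 30-180 days.

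The stake is interpretation. The comparison with unilateral stimulation is the newer part of the question. A non-significant result there, read under a stated 80% power, could be taken as evidence that one-sided stimulation does as well, although the power for that contrast may be far lower.

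**Working it through.** **1. The plan's own figure.** 60/(1 - 0.20) = 75, rounded up to a multiple of four: 76 = 4 x 19. The dropout step is correct. N = 60 itself cannot be reproduced, because no effect, SD or test is given. The effect is therefore back-solved from 80% power at N = 60 in two ways. Both are assumptions.

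**2. Route A: N = 60 gives 80% for one pairwise t-test, 15 versus 15.**
Power = P(T > t(1 - a/2, df)), with T noncentral t and noncentrality d x sqrt(n/2).
- 80% at a = 0.05 and df 28 needs d = 1.06; noncentrality = 1.06 x sqrt(7.5) = 2.90.
- Six pairs, a = 0.0083: critical value 2.84 (df 28) gives 53.3%; 2.74 (pooled ANOVA error, df 56) gives 56.9%.
- Normal approximation, which does not depend on the scale of the outcome: Phi(1.960 + 0.842 - 2.638) = Phi(0.164) = 56.5%.
- Three pairs, a = 0.0167: 64.0% (df 28) or 66.8% (df 56).
- No dropout, 19 per arm, six pairs, same d: 68.1% or 70.9%.

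**3. Route B: N = 60 gives 80% for the four-arm F-test.**
Noncentral F with 3 and 56 df and noncentrality f² x 60; 80% needs f = 0.441. Since f is the SD of the four means divided by the within-arm SD, a pattern of means fixes each pairwise d. Example: for combined, unilateral, unilateral, sham = 1, 0.5, 0.5, 0, the SD of the means is sqrt(0.5/4) = 0.354. Combined versus sham is then d = 0.441/0.354 = 1.25, and combined versus a unilateral arm is half that, 0.62. Power uses the pooled error.

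| Pattern of means | Contrast | d | Alpha 0.05 | 3 pairs | 6 pairs | 6 pairs, 19 per arm |
|---|---|---|---|---|---|---|
| Only combined differs | combined vs any arm | 1.02 | 78% | 63% | 53% | 67% |
| Unilateral arms midway | combined vs sham | 1.25 | 92% | 83% | 75% | 87% |
| | combined vs each unilateral | 0.62 | 39% | 23% | 16% | 22% |
| Equally spaced | combined vs sham | 1.19 | 89% | 78% | 69% | 82% |
| | combined vs farther unilateral | 0.79 | 57% | 39% | 29% | 40% |
| | combined vs nearer unilateral | 0.40 | 19% | 9% | 6% | 7% |
| Two arms equal above two equal | combined vs an arm that differs | 0.88 | 66% | 49% | 38% | 51% |

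**4. What restricting the family achieves (15 per arm, pooled error).**
- d = 1.06 against every arm: Bonferroni over six pairs 57%; Dunnett with combined as reference (critical value about 2.41) 69%; fixed sequence at 0.05: 81% at the first step, then 71%, then 64%.
- Unilateral arms midway: the first step has 92%, but each unilateral contrast has only 39% even at an unadjusted 0.05, so no later step can exceed that.

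**The case against.** The strongest reply is that the shortfall is inferred. The section does not say that N = 60 came from a pairwise test, does not say that 0.05 was per comparison, and is a condensed account. The Bonferroni sentence does not count the pairs. The plan also includes a two-factor repeated-measures ANOVA, which might be the sized test and might be more precise. Much of this stands, and it limits what can be claimed:

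- **A reader might infer that power is 53-57% at best.** That range holds only on Route A with six pairs. Route B gives up to 75% for combined versus sham over six pairs, 83% if only three pairs are corrected for, and 82-87% over six pairs in two of the patterns if nobody drops out.
- **A reader might infer that the other three pairs only waste alpha.** The Abstract sets out to compare several regimens and to help find the best one. Low-frequency versus sham, high-frequency versus sham and low- versus high-frequency fit that purpose.
- **A reader might infer that the trial will probably miss a real benefit.** That depends on a true effect the documents do not give. The plan makes no equivalence claim, and its limitations paragraph calls the sample small.

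The core survives. Appealing to the omnibus or repeated-measures test does not rescue the aim: a significant F does not show that combined beats sham or either unilateral arm, and the unilateral contrasts do worst on that route. If any single contrast has 80% power at 0.05, moving it to 0.0083 costs about the same whatever the outcome scale.

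**Conclusion.** The point holds in conditional form. The stated 80% at an unadjusted two-sided 0.05 does not describe the Bonferroni-tested contrasts in the aim. At the planned 15 evaluable per arm with six pairs, no scenario tried reaches 80%; the highest is 75%, for combined versus sham. The range is 53-57% if N = 60 was sized on one pair. If it was sized on the four-arm F-test, it is about 38-75% for combined versus sham and 6-53% for combined versus a unilateral arm that differs from it.

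This rests on three assumptions: an effect back-solved from the stated power, correction over all six pairs (the plain reading, though not written), and dropout at the planned 20%. Relaxing the last two narrows the gap and can close it for combined versus sham on the F-test route, but for no unilateral contrast in the scenarios tried. The dropout arithmetic is not in question.

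**What to change.** 1. **Restate the Sample size section (the essential part).** Give the test and assumed effect behind N = 60, and the power of each of the three contrasts in the aim at the alpha actually used. Say what the high-frequency contrast is based on, since the cited source, as described, offers nothing for it.
2. **Before unblinding, name the three FMA-UE contrasts as the confirmatory family.** Test them in fixed order at two-sided 0.05 with combined versus sham first, or by Dunnett with combined as reference. Report the other three pairs as secondary.
3. **State how a null result will be read.** A non-significant combined versus unilateral result must not be interpreted under a stated 80% power.

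**Cost.** No extra patients, but a less favourable stated power, no confirmatory claim for the other three pairs, and a documented amendment to a registered, ethics-approved trial that is already running. A reader might expect step 2 to restore 80%. It does so only for the first step of the sequence, and only if the effect is as large as d = 1.06. Keeping six-pair Bonferroni with 80% per pair on Route A would instead need about 23-25 evaluable per arm, which is 29-32 per arm after 20% dropout, or 116-128 in total.

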### Randomization

After meeting the inclusion criteria, 76 subjects will be randomly assigned in a 1:1:1:1 ratio to the LF-HF-rTMS, low-frequency, high-frequency, and sham stimulation groups. The grouping will be performed according to a PC-generated random number, which will be concealed in a sealed envelope. The random sequence will be managed and supervised by specific personnel who have no contact with the subjects and are not included in data collection or analysis.

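### The stated 80% power is set at an unadjusted 0.05 and is not tied to the Bonferroni-corrected arm comparisons that answer the trial's question; if sized at that level, it does not hold for all three of them

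*Protocol article*

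**What the plan says.** The Sample size section takes FMA-UE from an earlier published trial as the basis. The significance level is "specified as a two-sided test with *α* = 0.05". Power is stated separately, "with a degree of certainty (test efficacy1-β) of = 0.8", and the result is 60 patients before any allowance for loss. Dropout is then added: "Considering a 20% dropout rate and the average distribution of each group, the total sample size was 76". Under Randomization, "76 subjects will be randomly assigned in a 1:1:1:1 ratio", so 60 evaluable patients means 15 per arm and 76 means 19. The section gives no effect size or standard deviation, does not name the powered test, and does not mention multiplicity.

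The last paragraph of the Background sets the question: outcomes after combined stimulation "compared with that by sham and unilateral hemispheric stimuli". That is three contrasts: combined against sham, against low frequency and against high frequency.

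Data analysis plans a one-way ANOVA between groups with "Bonferroni correction for post hoc comparisons between groups". It does not say how many comparisons share the correction. All pairs of four arms would be six; the contrasts in the aim would be three.

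**The concern.** The article itself states both the alpha used for sizing and the stricter rule for the arm comparisons, and the two do not match. A four-arm F test can be significant without showing whether combined stimulation beats sham or either unilateral arm; only the corrected comparisons show that. The only power figure in the article is therefore not tied to the tests that answer its question.

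The consequence lies in interpretation. A reader who takes 80% as the chance of showing an advantage of combined over unilateral stimulation will read a non-significant corrected result as evidence against it, when the trial may have had little chance of showing the assumed effect.

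**Working it through.** **Inputs from the protocol article.** Two-sided alpha 0.05, power 0.80, 60 evaluable, 20% dropout, 76 randomised (Sample size); equal allocation to four arms (Randomization); ANOVA then Bonferroni (Data analysis); three contrasts of interest (Background).

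**Assumed, because not given.** The effect size (solved for below), the number of comparisons m (3 or 6), and the pattern of the four means.

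**Step 1: the plan's own figures.** 60 / (1 − 0.20) = 75; the next multiple of 4 is 76 = 4 × 19, so the inflation reproduces. The 60 cannot be reproduced without an effect size and a test.

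**Step 2: the effect that gives 80% at 60 patients and alpha 0.05.**
- Four-arm F test: degrees of freedom 3 and 56, noncentrality 60f². Power 0.80 gives f = 0.441.
- Two-sample t test, 15 per group: d = 1.06.
- Two-sample t test, 30 per group (60 read as a two-group total): d = 0.736.

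The t-test readings are included because the term two-sided suits a two-group test better than an F test.

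**Step 3: pairwise differences implied by f = 0.441 (SD units).**
- Two extreme arms, the others midway: largest pair f√8 = 1.25; each extreme against a middle arm, half of that, 0.62.
- Equally spaced: largest pair 6f/√5 = 1.18.
- One arm differs from three equal arms: 4f/√3 = 1.02.
- Two arms against two: 2f = 0.88.

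**Step 4: corrected power at 15 per arm.** Noncentral t with noncentrality d√(15/2), pooled error df 4 × 15 − 4 = 56, two-sided alpha 0.05/m. Critical t is 2.735 for m = 6 and 2.468 for m = 3. For example, d = 1.02 gives noncentrality 2.79.

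| Reading and contrast | d | m = 6 | m = 3 |
|---|---|---|---|
| F test, two extremes: largest pair | 1.25 | 75% | 83% |
| Same pattern: extreme vs middle arm | 0.62 | 16% | 23% |
| F test, equally spaced: largest pair | 1.18 | 69% | 78% |
| F test, one arm differs | 1.02 | 53% | 63% |
| F test, two vs two | 0.88 | 38% | 49% |
| t test, 15 per group | 1.06 | 57% | 67% |
| t test, 30 per group | 0.736 | 25% | 33% |

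The largest pair therefore runs from about 25% to 75% with six comparisons and from 33% to 83% with three. In the first two rows, if combined and sham are the extremes, combined versus sham has 75% or 83% and combined versus each unilateral arm only 16% or 23%.

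**Step 5: all three contrasts.** For a fixed f, the smallest advantage of the combined arm over the other three is greatest when those three are equal, because spreading them below the best of them uses up variance without raising that advantage. On the F-test reading the weakest contrast is thus at most 1.02 SD, with at most 53% (six) or 63% (three) power. On the t-test readings a contrast at the assumed difference has at most 57% or 67%. None reaches 80% for each of the three. The simulated chance of winning all three at 15 per arm is about 28% (six) or 39% (three) when only the combined arm differs, and about 7% or 11% when the unilateral arms lie midway.

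**Step 6: detectable difference and no dropout.** Solving the Step 4 formula for 80% at 15 per arm gives 1.31 SD (six) or 1.21 SD (three), against 1.04 SD uncorrected. With 19 per arm (df 72) it gives about 1.16 SD or 1.07 SD. At 19 per arm the largest pair in the two-extremes pattern has 87% or 92%, while with one arm differing each contrast has 67% or 75%.

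**The case against.** The strongest reply is that the 80% may be right for what it describes. Powering an omnibus ANOVA and following it with corrected post hoc tests is common, and it matches the order in Data analysis. The Sample size section does not claim 80% for any pair of arms. This stands: the figure cannot be called wrong, only unattached to the contrasts in the aim.

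Second, a reader might infer that no corrected comparison reaches 80% on any reading. The article does not support that. It leaves the number of comparisons open; with three, and with combined and sham at the extremes, combined versus sham reaches 83%.

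Third, every power figure above rests on an effect solved backwards. Had the software been run at the corrected level, power would be 80% by construction at 1.31 SD (six) or 1.21 SD (three). The stated 0.05 argues against this but does not exclude it. Intention-to-treat analysis of all 76 would also raise power, although the 80% is stated at 60.

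Finally, the article condenses a fuller protocol, so the missing effect size and test name are not in themselves a fault, and the limitations paragraph already admits a small sample. That admission does not say which comparisons are affected or by how much.

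**Conclusion.** The point holds in conditional form. The article states 80% at an unadjusted two-sided 0.05 and tests the comparisons of interest at a stricter level that the sizing does not mention. If 60 was obtained at 0.05, whether for the F test or for a two-group t test, no reading gives 80% for all three contrasts in the aim. The shortfall is largest for combined versus unilateral when the unilateral arms fall between combined and sham.

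The range of 25% to 75% should not be read as the power of the trial's comparisons in general. It applies to the largest pair under six comparisons, with a back-solved effect, 15 evaluable per arm and a common SD; three comparisons move it up, and smaller contrasts fall below it. Nor does the point show that 76 is the wrong number of patients: the dropout arithmetic is sound, and 60 cannot be tested without an effect size.

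**What to change.** In Sample size:
- Say which test the 80% refers to, with the effect size and SD behind it, and do not present it as the power of the arm comparisons.
- Give the corrected power for combined versus sham and combined versus each unilateral arm at 15 and 19 per arm, or the detectable difference: at 15 per arm about 1.31 SD for six comparisons or 1.21 SD for three; at 19 about 1.16 SD or 1.07 SD.

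In Data analysis:
- Fix the number of comparisons under the Bonferroni correction: three to match the aim, or six for all pairs.
- State that a non-significant corrected combined-versus-unilateral contrast will be reported as an estimate with its confidence interval and not read as evidence of no difference.

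This needs no extra patients and no change to the conduct of the trial. The only cost is a less favourable stated power. Because recruitment is under way, the number of comparisons should be fixed before unblinding.
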